### Patient management

Daily patient management will follow the ABCDE bundle [24]. Once respiratory and circulatory stability is achieved, continuous sedation will be discontinued as early as possible, followed by a spontaneous awakening trial. Subsequently, a spontaneous breathing trial will be performed, and readiness for weaning from mechanical ventilation will be assessed daily. Delirium will be managed primarily through adequate analgesia and restoration of the circadian rhythm, than pharmacological interventions whenever possible. However, if agitation persists despite these measures, pharmacological therapy will be considered. Furthermore, as described earlier, physicians, nurses, and physical therapists will collaborate and communicate closely to plan rehabilitation, with early mobilization implemented as part of standard care.

### Nutrition protocol

In this study, the day of ICU admission will be designated as Day 0, with the following day as Day 1. Nutritional therapy is delivered primarily via enteral nutrition in all eligible patients. All patients will receive small-volume nutrition on Days 1 and 2 (10–20 mL/h). On Days 3 and 6, resting energy expenditure (REE) will be measured using indirect calorimetry. Based on these measurements, the target for total caloric intake will be set at 70% of REE from Days 3 to 5, and increased to 100% of REE from Day 6 onward [9]. Nutritional support will be delivered continuously for 21 h per day, with a 3-h interruption, until the patient begins oral intake.

Protein requirements will be calculated based on the patient’s usual body weight prior to ICU admission. In patients with obesity (body mass index ≥ 30 kg/m^2^), protein targets will be calculated using ideal body weight, defined as the body weight corresponding to a BMI of 22 kg/m^2^.

For nutrition planning, both the type and volume of formula will be automatically determined using an Excel-based tool with VBA macros, incorporating measured REE, the target protein dose, and the infusion rate of propofol at the time of planning. The tool will search for a combination in which both energy and protein intake fall within 100–110% of the targets. If no feasible combination is identified, the output will be left blank, and the final prescription will be determined at the discretion of the attending physician, who will also aim to achieve 100–110% of the targets for both energy and protein intake. This Excel-based tool was developed for clinical implementation to standardize nutritional prescriptions and does not represent a novel measurement or analytical method. Formal validation against external reference standards has not been performed; however, all calculations are based on established nutritional formulas and routinely collected clinical data.

Preparation and delivery of nutritional formulas will be performed by ICU nurses or dietitians who are not involved in outcome assessment. Participants and outcome assessors will remain blinded to group allocation throughout the study period. Given that differences in protein dose are not visually apparent at the bedside and that nutritional delivery follows standard clinical workflows, blinding is considered feasible and robust. Attending physicians are aware of the assigned protein targets for clinical safety reasons but not involved in outcome assessment.

If clinical circumstances such as persistent shock, gastrointestinal intolerance, or diarrhea necessitate modification of nutritional support, or if initiation or escalation of feeding is delayed, the attending physician may revise the plan using indirect calorimetry and the planning tool, based on the prevailing conditions. The protein source was not protocolized and followed standard clinical practice; however, the same commercially available enteral formulas were used in both groups, and no systematic differences in protein source (e.g., whey- vs. casein-predominant formulations) were intended between groups. The intervention targeted protein dose rather than protein composition. When enteral nutrition alone is insufficient to meet energy requirements, commercially available parenteral nutrition formulations containing amino acids may be used in accordance with standard ICU practice. Isolated amino acid infusion will not be used, as achieving the target protein dose via amino acid infusion would require excessive fluid volume and may increase the risk of volume overload. Dextrose-only parenteral nutrition will not be used. Adjustment of protein delivery will be primarily achieved through enteral nutrition formula selection and/or supplementation with protein powder.

Indirect calorimetry is limited in specific clinical situations, such as patients with chronic obstructive pulmonary disease, high levels of positive end-expiratory pressure, or high inspired oxygen fractions. However, it is considered the most accurate method for estimating energy expenditure in mechanically ventilated ICU patients and is therefore used whenever technically feasible. These limitations are acknowledged, and measurements will be interpreted in the context of the patient’s clinical condition. For patients receiving ECMO, REE will be estimated as 20 kcal/kg because indirect calorimetry is less reliable in this setting [9].

Renal function will be monitored daily during the intervention period using serum creatinine levels, urine output, and blood urea nitrogen.

The type and volume of enteral nutrition administered are routinely documented in the electronic medical records and daily temperature charts as part of standard ICU care. Actual daily protein intake will be calculated from these records to assess adherence to the assigned protein and calorie target. Adjustments to protein delivery may be made by the attending physician based on clinical conditions such as intolerance or renal deterioration; the actual delivered protein dose will be documented and analyzed.

Details of how nutrition delivery, mobilization, and safety parameters are routinely monitored and documented as part of standard ICU care are summarized in Table 1.

**Table 1 Tab1:** Routine monitoring and documentation of nutrition delivery, mobilization, and safety parameters

Domain	What is monitored	How it is documented	Clinical oversight
Protein delivery	Daily protein intake (g/kg/day)	Electronic medical record (nutrition orders and intake records)	Adjusted by attending physician based on clinical condition
Energy delivery	Daily caloric intake (kcal/kg/day)	Electronic medical record / nutrition chart	Managed as part of routine ICU care
Mobilization	Frequency and type of mobilization sessions	Physical therapy and nursing notes in the medical record	Conducted according to patient tolerance

Protein tolerance and gastrointestinal intolerance (e.g., vomiting, diarrhea, abdominal distension, or interruption of enteral feeding) are routinely assessed and documented as part of standard ICU nursing and medical records.

### Interventions

The intervention in this study will not involve differences in the intensity or frequency of rehabilitation; the focus will be on modifying protein intake between the two groups. In the control group, nutritional support will target the lower limit of protein intake recommended in current guidelines (1.2 g/kg/day) [9, 10]. In contrast, participants in the intervention group will receive a higher protein intake of 1.8 g/kg/day. As described previously, both caloric and protein intake will be adjusted to remain within 100–110% of the prescribed targets. Although European Society for Clinical Nutrition and Metabolism guidelines suggest higher protein targets for selected populations, such as trauma or obese patients [9], the present trial is not designed to individualize protein prescription based on diagnostic subgroups, but rather to evaluate the effect of two predefined protein targets under standardized mobilization conditions. Randomization is expected to distribute such patient characteristics evenly between groups.

The core intervention period will continue from Day 3, when protocolized protein delivery is initiated, until ICU discharge, death, or the initiation of oral intake, whichever occurs first, for a maximum of 28 days from randomization. During this period, standardized high-intensity mobilization will be provided as part of routine ICU care to all eligible patients.

### Randomization

Written informed consent will be obtained from patients who are expected to require mechanical ventilation for > 48 h. Once consent is obtained, randomization will be performed. The consent process will be completed within 24 h of initiating mechanical ventilation.

Randomization will be conducted using a variable block method, with block sizes of four, six, or eight selected at random, and patients will then be allocated to the two groups in a 1:1 ratio. Allocation will be performed by an independent third party who is not involved in clinical care or data analysis. To ensure allocation concealment, clinical staff will be informed of the assigned group only after patient enrollment.

### Blinding and masking procedures

This trial will employ a participant- and assessor-blinded design, in which participants remain unaware of their group allocation. Physicians and nurses cannot be blinded owing to the nature of the intervention; however, the primary outcome, FIM motor score, will be assessed by an independent physical therapist who is blinded to group assignment, thereby ensuring assessor blinding. The assessor will be an experienced clinician routinely involved in FIM evaluation.

### Sample size estimation

Our previous study was the first to investigate early mobilization of ICU patients using an MPL [22]. However, because the primary outcome in the present study differs, no optimal prior data are available to directly inform the sample size calculation. Therefore, we referred to previous studies on post-stroke patients and adopted a standard deviation (SD) of 20 and a minimal clinically important difference of 17 for the FIM motor score [25].

As there is no established SD or MCID for the FIM motor score at hospital discharge for mechanically ventilated ICU survivors, we used estimates from the post-stroke rehabilitation literature, where FIM is most extensively validated. Variability in ICU survivors may plausibly be larger owing to heterogeneity in diagnoses and ICU-related factors (e.g., sedation, delirium, complications), which could lead to underpowering; however, the direction and magnitude of this difference are uncertain.

The sample size was calculated using Power and Sample Size Calculation software (PS, version 3.1.2, Vanderbilt University, Nashville, TN, USA). With a two-sided *α* of 0.05 and *β* of 0.95, the required sample size was 37 patients per group, yielding a total of 74. To account for an anticipated 15% dropout rate, the final sample size was set at 90 participants.

The feasibility of recruiting 90 participants over ~ 20 months is supported by prior experience from our previous single-center MPL study in the same ICU, in which 92 patients were enrolled within approximately 20 months [22].

### Data collection

Baseline characteristics will be collected at the start of the intervention, and will include demographic and clinical data: age, sex, body mass index, primary diagnosis, and comorbidities assessed using the Charlson Comorbidity Index [26]. Severity of illness will be measured using the Acute Physiology and Chronic Health Evaluation (APACHE) II score. Additional clinical variables will include the presence of acute kidney injury (AKI) according to the Kidney Disease: Improving Global Outcomes criteria [27], presence of diabetes, score on the Malnutrition Universal Screening Tool [28], and the presence of malnutrition defined by the Global Leadership Initiative on Malnutrition criteria [29]. Furthermore, body composition will be assessed at enrollment using a bioelectrical impedance analyzer (InBody BWA2.0S; InBody Japan, Tokyo, Japan) to determine parameters including skeletal muscle mass, skeletal muscle index, fat-free mass index, and phase angle. Baseline FIM scores will not be collected because most patients are unable to undergo functional assessment at ICU admission due to sedation, mechanical ventilation, or impaired consciousness. Therefore, FIM was assessed only at hospital discharge, consistent with the study objective of evaluating post-ICU functional recovery.

Nutritional data will include the number of days from admission to initiation of enteral nutrition, the number of days until the target protein dose was achieved, and the mean intake of caloric, protein, parenteral caloric, enteral caloric, parenteral amino acid, and enteral protein during the intervention period. These data will be analyzed separately for Days 0–1 and from Day 3 onward.

Rehabilitation-related data will include the number of days from admission to initiation of mobilization, number of days mobilization was performed, and the ICU Mobility Scale score at ICU discharge [30].

In addition, treatment-related data will include the use of renal replacement therapy, use of ECMO, and the duration of mechanical ventilation.

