### Outcome

The primary outcome will be the total motor domain score of FIM at hospital discharge. The FIM motor score at hospital discharge was selected as the primary outcome because it represents the earliest clinically stable time point at which the cumulative effects of ICU-based interventions can be meaningfully assessed. FIM at ICU discharge may be influenced by non-clinical factors such as bed availability and transfer policies, and may underestimate functional recovery due to ongoing critical illness and sedation effects. In contrast, longer-term follow-up after discharge is more susceptible to loss to follow-up and confounding by post-ICU rehabilitation and social factors. Therefore, assessment at hospital discharge was considered the most appropriate balance between clinical relevance, feasibility, and internal validity.

Secondary outcomes and their assessment time points will be as follows:At ICU discharge: Functional Status Score for the ICU [31], Medical Research Council (MRC) score, and ICU length of stay.At 14 days after ICU discharge: FIM motor, cognitive subscale of FIM (FIM cog), Mini-Mental State Examination (MMSE), body composition parameters, MRC score, and Brief Pain Inventory (BPI).At hospital discharge: MRC score, FIM cog, body composition parameters, BPI, length of hospital stay, and mortality.At 60 days after hospital discharge: FIM motor score, MRC score, FIM cog, MMSE score, body composition parameters, and BPI.

Follow-up at 60 days post-discharge will be conducted during an outpatient visit scheduled at the time of discharge. For patients who die or cannot be assessed owing to severe consciousness disturbance, the FIM motor and FIM cog will be recorded at their minimum values (13 and 5, respectively), the MRC score will be assigned as 0, and the BPI will be recorded as missing. For patients who die before hospital discharge, FIM scores will be assigned as the minimum possible values (motor score 13 and cognitive score 5). This approach reflects that death represents the worst possible functional outcome and ensures that mortality is appropriately incorporated into the analysis of functional recovery rather than treated as missing data.

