### Statistical analyses

After data collection is complete, continuous variables will be presented as mean ± SD or as median with interquartile range (IQR), and categorical variables as numbers with percentages. Baseline characteristics and study outcomes will be compared between groups using the Student’s t-test or Mann–Whitney *U* test for continuous variables, and the chi-square test or Fisher’s exact test for categorical variables. All outcome analyses will be conducted according to the intention-to-treat principle.

The primary analysis will compare outcomes between groups according to the intention-to-treat principle.

As a sensitivity analysis, analysis of covariance (ANCOVA) will be performed to explore the robustness of the primary findings to variability in intervention implementation. As the actual duration of high-protein nutrition and high-intensity mobilization may vary among participants despite randomization, these variables will be included as covariates to account for differences in intervention exposure rather than to adjust the primary treatment effect.

Covariates included in the ANCOVA will be pre-specified based on clinical relevance and trial design considerations, not selected in a data-driven manner. Importantly, these analyses are intended as exploratory sensitivity analyses to aid interpretation of the results and will not replace the primary intention-to-treat comparisons.

Furthermore, sensitivity analyses will be performed with adjustment for the presence of acute kidney injury and use of renal replacement therapy (RRT).

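### Body composition is measured at enrolment, but the stated follow-up comparisons do not adjust for that value; this costs precision in secondary outcomes (minor)

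*Protocol article*

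**What the plan says.** Under Data collection, the protocol article states that "body composition will be assessed at enrollment using a bioelectrical impedance analyzer", yielding "parameters including skeletal muscle mass, skeletal muscle index, fat-free mass index, and phase angle". The same section explains why no baseline FIM is taken. That explanation does not extend to body composition, which does have a baseline.

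Under Outcome, body composition is a secondary outcome at three later times: 14 days after ICU discharge, hospital discharge ("MRC score, FIM cog, body composition parameters, BPI, length of hospital stay, and mortality") and follow-up ("At 60 days after hospital discharge: FIM motor score, MRC score, FIM cog, MMSE score, body composition parameters, and BPI").

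Under Statistical analyses, one general rule covers continuous variables: "Baseline characteristics and study outcomes will be compared between groups using the Student’s t-test or Mann–Whitney" test. Two sets of adjusted analyses follow, both as sensitivity analyses. One is an ANCOVA on the actual durations of high-protein nutrition and of mobilization. The other adjusts for AKI and RRT. The enrolment body composition value is not named as a covariate, no change score is defined, and the value is not among the variables listed for the imputation model.

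**The concern.** The trial's rationale is that extra protein supports muscle when combined with mechanical loading. Body composition is its only measure of muscle quantity; the MRC score measures strength. A patient's own starting value is likely to be among the best available predictors of the later value, yet the analysis as described does not use it. The durations that the ANCOVA does adjust for arise after randomization.

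Two things are at stake for these secondary outcomes. The confidence intervals may be wider than the collected data require. A chance difference between arms at enrolment would also pass partly into the follow-up contrast. Randomization uses variable blocks with no stratification described, so sex and body size are balanced only on average.

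**Working it through.** **Inputs from the article.** Two-sided alpha 0.05; power 0.95 (printed as β); SD 20 and difference 17 for FIM motor; 37 per group, 74 in total, 90 after 15% dropout; 1:1 allocation. No SD, effect, correlation or power is given for body composition.

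**The plan's own figure.** The normal approximation gives n per arm = 2 × [20 × (1.960 + 1.645) / 17]² = 35.97, so 36. The t-based solution is 36.96, so 37, as stated. Allowing for dropout, 74 / 0.85 = 87.1, so 88, against the 90 stated. These figures concern FIM motor. Here they only supply a plausible range of 37 to 45 per arm (90 / 2 = 45).

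**Unadjusted comparison.** In units of the between-patient SD, the difference detectable with 80% power is (1.960 + 0.842) × √(2/n). This is 0.65 SD with n = 37 and 0.59 SD with n = 45.

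**Adjusted comparison.** With ANCOVA on the enrolment value, the residual variance is (1 − r²) times the unadjusted variance. The SE ratio is therefore √(1 − r²), and the equivalent sample-size multiplier is 1/(1 − r²). The values of r below are assumptions.

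| r | 1 − r² | SE ratio | SE cut | Sample multiplier | Detectable, 37/arm | Detectable, 45/arm |
|---|---|---|---|---|---|---|
| 0 (unadjusted) | 1.00 | 1.000 | – | 1.00 | 0.65 SD | 0.59 SD |
| 0.3 | 0.91 | 0.954 | 5% | 1.10 | 0.62 SD | 0.56 SD |
| 0.5 | 0.75 | 0.866 | 13% | 1.33 | 0.56 SD | 0.51 SD |
| 0.7 | 0.51 | 0.714 | 29% | 1.96 | 0.47 SD | 0.42 SD |
| 0.8 | 0.36 | 0.600 | 40% | 2.78 | 0.39 SD | 0.35 SD |

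The percentage cuts do not depend on n. The detectable differences do, and they ignore the degree of freedom spent on each covariate.

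**Chance imbalance.** The enrolment means of the two arms differ by chance with a standard deviation of √(2/37) = 0.23 SD, or √(2/45) = 0.21 SD. An unadjusted follow-up contrast carries r times that imbalance. With r = 0.7 and 37 per arm, an imbalance of one standard error moves the result by 0.7 × 0.23 = 0.16 SD.

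**Change scores as an alternative.** With equal SDs, the variance of a change score is 2(1 − r) times the unadjusted variance: 1.4 at r = 0.3, 1.0 at 0.5, 0.6 at 0.7 and 0.4 at 0.8. The ANCOVA factor is smaller at every one of these values.

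**Is the covariate legitimate?** Consent is completed within 24 h of starting ventilation, and randomization follows. All patients receive the same small-volume feeding on Days 1 and 2, and protocolized protein starts on Day 3. The enrolment reading therefore precedes the dose contrast.

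**The case against.** The strongest reply is that one generic sentence in a condensed article covers every continuous variable, and that the covariates for a single secondary outcome belong in the analysis plan. Part of this stands. The article does not say whether body composition is analysed as an absolute value or as a change, and a t-test fits either. But the article is not merely silent: it names the tests and it names the adjustment variables, and the enrolment value is not one of them. ANCOVA is also at least as precise as either reading of the t-test, apart from the small cost of estimating the coefficient.

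A second reply is that impedance in acutely ill patients may be distorted by fluid shifts, particularly as ECMO patients are eligible and RRT is anticipated. That stands as a limit on the gain, and it is why r = 0.3 belongs in the range. It is not a reason against ANCOVA, which weights the baseline by its observed association.

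Some stronger readings are tempting but lack support in the document:

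- A reader might infer that body size and sex overwhelm any protein effect. No SD, correlation or expected effect is given. The body-size argument fits mainly absolute muscle mass: two of the named parameters are size-normalized indices, and phase angle is not a mass.
- A reader might infer that follow-up values cannot answer a question about muscle preservation. Under randomization, the arm difference in follow-up values and the arm difference in change have the same expectation.
- A reader might assume that the same analyzer is used throughout. It is named only for enrolment.
- A reader might take body composition to be the only marker of the proposed mechanism. The article does not give it that role, and MRC strength is also a muscle outcome, assessed at four times.

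The planned subgroup analysis by sex would show sex-specific results, but it is not an adjustment.

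**Conclusion.** The point holds as a minor one, confined to secondary outcomes. The stated comparison is valid and unbiased. What is lost is precision, together with protection against chance imbalance at enrolment. The size of the loss cannot be fixed from the document. It runs from slight (5% of the standard error at r = 0.3) to substantial (40% at r = 0.8), depending wholly on an assumed correlation. The primary FIM motor analysis, the sample size and the main conclusion are untouched.

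**What to change.** For each body composition parameter at each of the three follow-up times, estimate the difference between arms by ANCOVA with that parameter's enrolment value and sex as covariates, and report it with its 95% CI. Keep the unadjusted comparison as descriptive. Add the enrolment value to the imputation model for these outcomes. The plan's existing provision for transformations or robust alternatives when ANCOVA assumptions fail can apply unchanged. It would also help to state whether the follow-up readings use the analyzer named for enrolment.

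The cost is a sentence or two of analysis text and one degree of freedom per covariate, with no added measurement. The article reports that no participant had been enrolled at submission. The change should be recorded before any outcome data are seen by arm.
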